	**STUDY PERIOD**					
	**Enrollment**	**Baseline**		**Exit**	**Follow-up**	
**TIMEPOINT**^*****^	***t0***	***t0***	***6 months***	***t1***	***t2***	***24 months***
**ENROLLMENT:**						
**Eligibility screen (incl. psychological distress)**	X					
**Project information**	X					
**Informed consent **	X					
**Allocation**^******^	X					
**INTERVENTIONS:**						
**3for1 components**		X	X	X		
**Control group**		X	X	X		
**ASSESSMENTS:**						
**Questionnaires:**						
Sociodemographic variables		X		X	X	
Motivation to work		X		X	X	
Job-search self-efficacy (JSSE)		X		X	X	
Psychological distress (K6)				X	X	
Health-related quality of life (EQ-5D)		X		X	X	
General health state (EQ-VAS)		X		X	X	
General well-being (WHO-5)		X		X	X	
Somatic symptom burden (SSS-8)		X		X	X	
Depressive symptoms (PHQ-9)		X		X	X	
Symptoms of anxiety (GAD-7)		X		X	X	
Mental health diagnoses		X		X	X	
Mental health treatment		X		X	X	
Social outcomes (SIX)		X		X	X	
Social inclusion (ESIS)		X		X	X	
Help-seeking (GHSQ; AHSQ)		X		X	X	
Self-stigma (SSMIS-SF)		X		X	X	
Intervention evaluation (IG only)				X		
**Structured interviews:**						
Sociodemographic variables / changes in these variables		X		X	X	
(Un-) Employment history		X				
Current/recent employment				X	X	
Attempts on re-employment		X		X	X	
Barriers to re-employment		X				
Mental health issues & treatment		X		X	X	
Health service utilization		X	X	X	X	
**Job center records:**						
Receiving benefits: yes vs. no				X	X	X
Duration of receiving benefits after study entry (in months)				X	X	X
**Database records (IG only):**						
Intervention utilization intensity (in minutes)				X		
Intervention component utilization intensity (in minutes)				X		

^*^t0: Enrollment and baseline assessment at the same timepoint, individual intervention period of 12 months for IG starting directly afterward; t1: exit interview and questionnaires 12 months after enrollment and baseline, and, for IG, directly after end of intervention period; t2: follow-up interview and questionnaires 18 months after enrollment and baseline, and, for IG, 6 months after end of intervention period

^**^Allocation based on enrollment timing in study: allocation of the first cohort to CG and the second cohort to IG

### Data collection and management

Assessments will be conducted via structured interviews and online questionnaires at all measurement points. We aim to conduct most interviews in person, but will conduct them via telephone if required and more practical. In particular, the interview six months after study entry on health service utilization will be conducted predominantly via telephone because its short duration would be disproportionate to the travel time to the research sites. Online questionnaires can be completed either on a tablet computer directly in the job center or via a link sent by e-mail. Paper-pencil-versions will be provided as well, in particular for rare technical issues, parallel assessments per research location, or participants with low technological proficiency. Research staff will assist questionnaire completion if needed.

We will employ multiple processes to ensure high quality and completeness of the collected data. Firstly, we selected established instruments for the questionnaires, many have been successfully used in a previous study in a similar population [61]. Regarding employed interview questions, they were discussed and assembled in an iterative process within our research team whose principal investigators have in-depth research experience in the topic area. Secondly, research staff will be trained to administer the questionnaires and conduct the interviews. They will be present when participants complete questionnaires and support them where needed. After measurement points, research staff will check the participants’ responses for completeness, data input mistakes, and apparent inconsistencies. If necessary, they will resolve these together with participants. Thirdly, research staff will meet regularly together with the project coordination and principal investigators to discuss the data collection and to clarify any open questions regarding special cases. This process will ensure high consistency in data collection across the different research sites. Finally, data quality checks will be performed on a regular basis by the biometrical experts within the research team to verify the completeness and plausibility of the data input in the database. Any anomalies in the database will be discussed and resolved within the research team.

### Statistical methods

For the analysis of the primary outcome, logistic regression analysis will be applied. Logistic regression analysis enables the prediction of the binary outcome (in employment: yes vs. no) based on the binary group status (CG vs. IG), while controlling for relevant covariates such as the job center that the participant is registered with, the unemployment rate of the respective districts, duration of unemployment and of receiving basic income support, as well as baseline demographic variables which are significantly different in the two groups. The secondary outcomes will be analyzed with varied analysis methods based on the characteristics of the data: For the hypotheses which propose differences in binary outcomes (i.e., Hypotheses 3–4), logistic regression analysis will be applied; for hypotheses that predict difference in continuous outcomes (i.e., Hypotheses 2, 5–8), we will apply analyses of covariance to compare the two study groups. To estimate the prevalence of increased psychological distress in job center clients that complete the screening measure, we will conduct a frequency analysis (i.e., Hypothesis 9).

Additionally, we will analyze the cost-effectiveness of the intervention from two perspectives: We will address the intervention’s cost effectiveness in terms of benefits of employment for the social welfare state. More specifically, we will balance the costs for the intervention with the reduced costs for basic income support and related social welfare benefits. Furthermore, we will evaluate the intervention’s cost-effectiveness by relating the incremental total costs of illness, including the direct costs of health service utilization and the indirect costs of productivity loss, to the incremental gain in quality adjusted life years (QALYs) [97, 98].

Analyses will be conducted using all observations with available data, applying an intention-to-treat-approach. Accordingly, participants will be treated as part of the group to which they were allocated at study enrollment. As the study spans over 1.5 years, we expect a certain degree of dropouts; we accounted for a 35% dropout rate between t0 and t1 in our power analysis. Research staff will make every reasonable effort to obtain as complete data as possible from as many participants as possible across all measurement points, especially regarding the primary outcome measure. To incentivize participation in the assessments, we will offer compensation for time and travel costs. At study enrollment, we will collect multiple ways to contact participants (i.e., postal address, phone number, mobile number, multiple e-mail addresses, contact information for significant others). After enrollment, we will maintain regular contact with participants to facilitate up-to-date contact information for the next assessment. If data cannot be collected at one measurement point after study enrollment (e.g., t1), we will attempt to collect data at the following measurement point.

In order to reduce missing data on individual items, participants will be notified of missing responses by the database and encouraged to provide complete responses. If questionnaires are answered on paper, research staff will review them immediately and ask the participant to complete any missing items. If items are still missing, we will use multiple imputation if up to 30% of item responses are missing; if a higher percentage is missing, no scale score is calculated.

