= at least 21 months in basic income support within the preceding 24 months).*Hypothesis 5: *Twelve months after study entry (t1), participants in the intervention group will report significantly higher levels of job-search self-efficacy than participants in the control group.*Hypothesis 6: *Twelve months after study entry (t1), participants in the intervention group will report significantly more favorable outcomes on various psychosocial measures (i.e., psychological distress, health-related quality of life, general health state, somatic symptom burden, depressive symptoms, symptoms of anxiety, social integration, self-stigma) in comparison to participants in the control group.*Hypothesis 7: *Twelve months after study entry (t1), participants in the intervention group will report significantly higher intentions to and past acts of seeking professional help for mental health issues than participants in the control group.*Hypothesis 8: *Eighteen months after study entry (t2), participants in the intervention group will report significantly more favorable outcomes on the secondary outcomes mentioned in Hypotheses 5-7 than participants in the control group.*Hypothesis 9: *Of those job center clients that complete the screening measure for psychological distress, at least 30% will report experiencing at least moderate psychological distress indicated by a score of nine or greater on Kessler’s Psychological Distress Scale – K6 version [58].^1^

Furthermore, to evaluate the feasibility, implementation, and sustainability of the intervention components as regular service in job centers, we will conduct qualitative interviews with relevant stakeholders (e.g., job center executive board members, employment advisors, intervention providers, and intervention participants). Finally, we will evaluate the cost effectiveness of the 3for1-intervention program.

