Despite the innovative and comprehensive approach of our intervention program, our study has certain limitations. Firstly, the study groups are not randomized, but allocated based on time. As the 3for1-intervention program includes active cooperation with the job centers’ employment advisors, we expect that the culture and way of working in the job centers themselves could be changed by the intervention. Therefore, a parallel CG could be biased by these changes, impeding the evaluation of the intervention’s actual effectiveness. However, the non-randomization could mean that the two groups differ on demographic variables and relevant outcomes at baseline. Additionally, as the recruitment phase for both groups will cover several years, there may be various developments in society and policies that could affect the two groups differently. We will collect a variety of covariates and use analysis methods that enable us to control for these covariates, such as logistic regression or analysis of covariance, to minimize bias in the estimation of the intervention effect [99]. Another challenge will be participant retention across the 1.5-year study period. If participants drop out of the study, conclusions from the analysis might be biased by selective dropout (e.g., less motivated participants, participants in CG without offered benefit of the intervention program). As described, we will make every reasonable effort to collect data from as many participants as possible across the study period. Additionally, we will analyze the data in terms of selective dropout effects. Finally, insufficient German language skills are an exclusion criterion. Consequently, the effectiveness of the intervention program can only be evaluated for a subsample of unemployed individuals with mental health issues. Therefore, we can only draw limited conclusions about its broader effectiveness for job center clients with mental health issues in general.

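### One ANCOVA per follow-up leaves the 12-month scores out of the 18-month test (H8), whose estimate can be biased if return at 18 months depends on those scores

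*Protocol article*

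**What the plan says.** Under Statistical methods, the protocol article assigns ANCOVA "for hypotheses that predict difference in continuous outcomes (i.e., Hypotheses 2, 5–8" and states that "we will apply analyses of covariance to compare the two study groups". No mixed or repeated-measures model is named anywhere.

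Under Objectives, each hypothesis is tied to one time point. H5 reads, for t1, that "participants in the intervention group will report significantly higher levels of job-search self-efficacy than participants in the control group"; H6 and H7 are also t1 hypotheses. H8 moves the same outcomes to t2: "participants in the intervention group will report significantly more favorable outcomes on the secondary outcomes mentioned in Hypotheses 5-7". Table 2 schedules the scales at both visits.

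On missing data, Statistical methods says "Analyses will be conducted using all observations with available data, applying an intention-to-treat-approach". For a person who misses a visit, "we will attempt to collect data at the following measurement point". Multiple imputation is described only for gaps within a questionnaire, up to 30% of its items. Nothing is stated for a visit missed altogether. The sample-size section anticipates 35% dropout by t1 and gives no figure for t1 to t2. The Discussion concedes that "conclusions from the analysis might be biased by selective dropout" and promises an analysis of selective dropout, without giving a method.

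**The concern.** An ANCOVA has one outcome at one time. Run at t2 on those seen at t2, it takes no information from the t1 score of anyone who attended at 12 months and then left. Run at t1, it takes none from people who missed t1 but were followed up at t2, as the plan intends.

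Lost efficiency is the smaller part of this. A person's state at 12 months may influence whether they come back at 18. If it does, beyond what the adjusted covariates explain, those seen at t2 are a selected group and the t2 comparison can be off. H8 is the plan's only stated test of whether gains on these scales last after the programme ends, and the scores that could correct for such selection would already be in the database.

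**Working it through.** **The plan's own figure.** There is no calculation for H5-H8 or for t2. The only one concerns the primary outcome (15% against 30%, two-sided 0.05, power 0.90):

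n = [1.960·√(2·0.225·0.775) + 1.2816·√(0.15·0.85 + 0.30·0.70)]² / 0.15² = (1.157 + 0.745)² / 0.0225 ≈ 160.8, so 161 per group; 161 / 0.65 = 247.7, so 248.

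Both stated figures reproduce. At t1 the plan implies 250 × 0.65 = 162.5 per group. If a further 10%, 20% or 30% is lost (my assumption), about 146, 130 or 114 per group have t2 data.

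**Which scores enter which test**

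| Seen at | t1 ANCOVA | t2 ANCOVA | Left unused |
|---|---|---|---|
| t1 and t2 | yes | yes | nothing |
| t1 only | yes | no | t1 score, for H8 |
| t2 only | no | yes | t2 score, for H5-H7 |
| neither | no | no | no follow-up score exists |

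**Estimators compared.** The ANCOVA regresses the t2 score on group and t0 score among those seen at t2. The joint estimate, which is the likelihood (mixed-model) answer when nobody returns after dropping out, is γ + β·δ. Here δ is the group coefficient for t1 given t0 among all seen at t1. γ and β are the coefficients of group and of the t1 score for t2, given t0, among those seen at t2.

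**Set-up A** (assumed: 250 per group; 35% lost at random by t1; correlations t0-t1 0.5, t0-t2 0.4, t1-t2 0.7; later loss either a flat 20% or with logit -1.5 ± 1.0 per SD of the score; 1,500 runs). Mean t2 estimates in SD units, ANCOVA / joint:

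| Loss after t1 depends on | True effect 0 | True t2 effect 0.30 (t1 effect 0.30) |
|---|---|---|
| nothing | 0.000 / 0.001 | 0.298 / 0.298 |
| t0 score | 0.001 / 0.001 | 0.306 / 0.304 |
| t1 score, same in both groups | 0.001 / 0.002 | 0.281 / 0.301 |
| t1 score, opposite by group | 0.201 / 0.003 | 0.475 / 0.296 |

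With a t1 effect of 0.50 and a t2 effect of 0.30, the third row becomes 0.267 / 0.301. Simulation error of each mean is about 0.115/√1,500 = 0.003. The joint estimate's standard error was 0-5% smaller (for example 0.107 against 0.111 with random loss and no effect).

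**Set-up B** (assumed: 65% seen at t1 and about 59% at t2; 14-16% seen at t1 only and 9% at t2 only; correlations 0.55, 0.50 and 0.65 in the same order; return at t2 depends on the t1 score in controls only, log-odds 0.5 or 1.0 per SD; 1,500 runs):

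| | log-odds 0.5 | log-odds 1.0 |
|---|---|---|
| True 0: ANCOVA / joint | -0.035 / 0.001 | -0.071 / -0.001 |
| True 0.30: ANCOVA / joint | 0.265 / 0.300 | 0.231 / 0.302 |
| ANCOVA rejection rate, no effect | 5.6% | 11.2% |
| ANCOVA power, effect 0.30 (0.83 without selection) | 0.75 | 0.61 |

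A repeat of this set-up gave ANCOVA biases of -0.037 and -0.074. The sign reverses if it is the better-off controls who leave. Without selective loss, the standard error at t2 was 0.0995 (ANCOVA) against 0.0964-0.0976 (joint), about 2-3% smaller.

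**Loss before t1.** When controls were lost before t1 according to the t1 score they would have had (log-odds 1.0 per SD, no true effect, 1,000 runs), the bias at t2 was -0.066 (ANCOVA) and -0.068 (joint). At t1 it was -0.22 and -0.20. The joint model hardly helps there.

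**The case against.** ANCOVA at a stated time point is a standard analysis and matches H5-H8 as worded. Several further objections are sound.

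- A reader might infer that separate ANCOVAs break the rule "Analyses will be conducted using all observations with available data". They do not. Every t1 score enters the t1 test and every t2 score the t2 test, which is what an available-case rule by allocated group requires.
- A reader might take the Discussion to expect that t1 scores will drive return at t2 differently by group. It says only that selective dropout might bias conclusions. Its examples are poorly motivated participants and controls not offered the programme, over the whole study; it does not mention t1 scores or loss after t1.
- The size depends on the mechanism. A bias of 0.04-0.07 SD is below one standard error (about 0.10). A rejection rate of 5.6% cannot be told from 5% with 1,500 runs (standard error √(0.05·0.95/1,500) = 0.6 percentage points).
- In set-up B about 26% of participants (100 - 65 - 9) have neither follow-up score, so no model can borrow for them.
- This is a condensed article. One ANCOVA per visit is an inference, and an unseen analysis plan may say more about missed visits.

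These points limit the claim without removing it. The article names the method, names no longitudinal model, and limits the imputation it describes to items. The promised dropout analysis is not described as changing the estimate. The joint model loses essentially nothing when dropout is harmless.

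**Conclusion.** The point holds in conditional form. On the natural reading, H8 is tested without the t1 scores of people lost after t1, and H5-H7 without the t2 scores of people who missed t1. The H8 estimate **can** be biased if return at t2 depends on the t1 score beyond the adjusted covariates. It would be wrong to say that dropout after t1 **does** bias the 18-month results, because the documents do not establish that mechanism.

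The likely size runs from about 0 to about 0.2 SD. Only opposite dependence in the two groups reaches the upper end. Dependence in controls only gives 0.04-0.07 SD, and equal dependence with a working treatment gives 0.02-0.03 SD. The correlations, the retention at t2 and the dropout models behind these figures are all assumptions. Only the 250 per group and the 35% loss by t1 come from the protocol.

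Only secondary outcomes are touched. The change is worth making because H8 carries the question of durability and the better analysis uses data already collected.

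**What to change.** For each continuous scale in H5-H8, fit one mixed model for repeated measures over t1 and t2. Include group, visit, group-by-visit, baseline value-by-visit and the planned covariates, with an unstructured covariance. Read H5-H7 from the t1 contrast and H8 from the t2 contrast. Keep the per-visit ANCOVAs as a sensitivity analysis. The yes/no items of the Actual Help-Seeking Questionnaire fall outside this change.

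The cost is analysis-plan wording and modest programming, with no new data. The model is slightly more complex and assumes that missingness is explained by observed scores and covariates. It does not repair loss before t1, or loss that depends on unobserved t2 values, and the plan should say so.

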Upon study entry, research staff will record detailed contact information from participants as well as their banking details for compensation, including written consent to use these details for said purpose. Subsequently, research staff will conduct an entry interview with participants and ask them to complete a questionnaire (i.e., baseline assessment, t0). After completing this baseline assessment, participants will be contacted for a short telephone interview after six months to assess health service utilization in the preceding six months, as well as after 12 months (i.e., t1) and 18 months (i.e., t2) for more in-depth assessment similar to the baseline assessment, including conducting an interview and completing a questionnaire. Additionally, research staff will ask participants’ written consent to request certain data from their job center records, specifically their status of receiving basic income support benefits (yes vs. no) and the duration of receiving full basic income support at 12, 18 and 24 months after study entry. Whether written consent for this additional data request is given or not will not affect study participation.

Figure 1 shows a flow chart for participants’ study experience.

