### Sample size

We aim to recruit 500 participants, 250 participants per group. Sample size calculation is based on the primary outcome measure at t1 (i.e., employment status 12 months after study entry). Based on a previous longitudinal observational study with unemployed individuals with mental health issues [61], we assume a re-employment rate of 15% with TAU. We aim to achieve a re-employment rate of 30% in the IG. We conducted an a-priori power calculation for this expected intervention effect [62]: Applying a two-sided significance level of α = 0.05 and a statistical power of 0.90, we estimated that *n* = 161 participants in each group are required to show this effect. Based on previous research projects in this subject area, we anticipate a dropout rate of 35% between t0 and t1. To test the intervention effect for the primary outcome, we accordingly require an initial sample size of at least *n* = 248 participants per group at t0.

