##### Integration of components

Each local intervention team consists of a 50% FTE psychologist/psychotherapist, an 80% FTE job coach, and four peer navigators on marginal part-time employment as intervention providers, as well as a 50% FTE researcher who conducts the study onboarding and data collections, and coordinates the local intervention providers. The researcher and intervention providers work as a local team with weekly team meetings where cases are discussed. All team members have equal rights and are encouraged to contribute their own perspective to the cases. Involving other component providers in the cases, where suitable, is encouraged to provide effective individualized support to participants.

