#### Primary outcome

The primary outcome is the proportion of participants who are in competitive employment in the primary labor market subject to social insurance contributions 12 months after study entry (yes vs. no). Competitive employment in the primary labor market refers to employment for which anyone can apply and which is not protected or accessible for individuals with disability status only. It will be assessed via self-report as part of the exit interview.

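### The primary analysis rests on available cases under an intention-to-treat label; with 35% loss expected, dropout that depends on employment differently by group can bias it in either direction.

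*Protocol article*

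**What the plan says.** - **Analysis set** (Protocol article, Statistical methods): "Analyses will be conducted using all observations with available data, applying an intention-to-treat-approach". The next sentence explains intention-to-treat as keeping participants in their allocated group.
- **Source of the primary outcome** (Primary outcome): "It will be assessed via self-report as part of the exit interview".
- **Expected loss** (Sample size): 35% between baseline and t1, met by raising the number per group from 161 to 248, with a target of 250.
- **Imputation** (Statistical methods): multiple imputation applies to missing questionnaire items, up to 30% of them. Nothing is stated for a missing employment status at t1.
- **Selective dropout** (Discussion): the authors warn that "conclusions from the analysis might be biased by selective dropout (e.g., less motivated participants, participants in CG without offered benefit of the intervention program"), and promise to analyse the data for such effects, without a method or a link to the primary estimate.
- **Other data collected:** job start and end dates are asked at both the exit and the follow-up interview (Secondary outcomes). With separate, optional consent, job-centre records are requested at 12, 18 and 24 months, "specifically their status of receiving basic income support benefits (yes vs. no") and the duration of full benefit (Participant recruitment and timeline).
- **Re-contact** (Statistical methods): after a missed visit, staff will try to collect data at the next one.

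**The concern.** A participant without an exit interview has no primary outcome and drops out of the comparison. Keeping the others in their allocated groups does not repair that. The remaining comparison is unbiased only if, after covariate adjustment, loss does not depend on employment differently in the two groups.

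The plan itself gives reason to doubt this, since it names control participants, who are offered no intervention, as possible dropouts. Contact also differs by group: intervention participants may use job coaching without a limit once in work during the 12 months (Job coaching), and those not using any component are regularly contacted (Adherence and auditing). The general retention efforts apply to everyone.

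At stake is the trial's main result. The plan fixes the analysis set, answers 35% loss only with more participants, and states no rule for using later information to fill the gap.

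**Working it through.** **1. The plan's own figures.** Inputs from Sample size: "we assume a re-employment rate of 15% with TAU"; "We aim to achieve a re-employment rate of 30% in the IG"; "Applying a two-sided significance level of α = 0.05"; power 0.90. With pooled variance and no continuity correction, the mean rate is 0.225 and

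n = [1.960·√(2·0.225·0.775) + 1.282·√(0.15·0.85 + 0.30·0.70)]² / 0.15² = 161 per group.

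161 / (1 − 0.35) = 247.7, so 248. Both figures reproduce.

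**2. What is missing.** At 250 per group, 250 × 0.65 = 162.5 are analysed and 87.5 are not: 175 of 500 in all. Power at 162.5 per group is 90.3%, so the inflation does what it was meant to do for power.

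**3. How far the missing could move the result.** Suppose completers show exactly 15% vs 30%. The full-cohort difference is 0.65 × 0.15 + 0.35 × (m_IG − m_CG), where m is the employed share among the missing.
- Worst cases: 0.0975 − 0.35 = −25.3 points and 0.0975 + 0.35 = +44.8 points.
- The difference is zero when m_CG exceeds m_IG by 0.0975 / 0.35 = 27.9 points.
- With m_CG = 25% and m_IG = 15%, it is 6.3 points (z = 1.70 at 250 per group, not significant).

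**4. Spurious effect when there is none.** Assumptions, not in the plan: the same true employed share p in both groups, 65% retained overall in each, and retention r_E among the employed. The observed rate is p·r_E / 0.65. The last column is the chance that a two-proportion test with 162.5 per group is significant in favour of the intervention; its nominal value is 2.5%.

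| p | r_E control / intervention | Observed control | Observed intervention | Difference (points) | Chance |
|---|---|---|---|---|---|
| 20% | 50% / 80% | 15.4% | 24.6% | +9.2 | 55% |
| 15% | 50% / 80% | 11.5% | 18.5% | +6.9 | 42% |
| 20% | 55% / 75% | 16.9% | 23.1% | +6.2 | 28% |
| 20% | 50% / 65% | 15.4% | 20.0% | +4.6 | 19% |
| 15% | 50% / 65% | 11.5% | 15.0% | +3.5 | 15% |

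The last two rows have selection in the control group only.

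**5. The opposite direction.** Let 20% be employed in both groups, with employed retention 65% in both and unemployed retention 55% in control and 65% in intervention. Control completers show 0.13 / (0.13 + 0.44) = 22.8% and intervention completers 0.13 / (0.13 + 0.52) = 20.0%. The bias is then 2.8 points against the intervention.

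**6. Counting the missing as not employed.** In the first row of the table this gives 0.20 × 0.50 = 10% vs 0.20 × 0.80 = 16% of 250: still a spurious 6 points, significant in about 51% of trials. It is no safeguard here.

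**The case against.** The strongest reply is that a condensed article leaves the handling of missing outcomes to the full protocol or analysis plan, that the text openly says available data and explains its use of intention-to-treat, and that the Discussion promises a dropout analysis. Silence on sensitivity analyses would indeed be no finding alone. What stands is the stated rule: the article fixes the analysis set, confines imputation to items, and leaves the promised dropout analysis unconnected to the primary estimate.

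Three stronger readings are tempting and not supported.
- **That the design builds in a bias favouring the intervention.** No passage says that employed control participants become unreachable. Coaching is voluntary, interviews can be done by telephone, and compensation and several contact routes apply to all. Step 5 shows the direction can reverse. The 50% / 80% case is strong selection: with p = 20% it forces unemployed retention of 68.8% in control and 61.3% in intervention, so the intervention group must lose more of its unemployed than control does.
- **That the plan ignores the other data.** It does plan re-contact at the next visit. It only fails to say that 12-month status will be derived from what is learned there.
- **That benefit records could replace or verify the self-report.** They show benefit receipt, not insured employment; consent is optional; and the inclusion criteria themselves recognise benefit that tops up earnings from insured employment.

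**Conclusion.** The concern holds in this form: the primary analysis is an available-case analysis, the intention-to-treat label covers allocation only, and the stated plan does not protect the primary estimate against dropout that depends on employment differently by group. The sample size is not in question.

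The size depends on retention by employment status, which the plan does not give. Under the assumed patterns in which employed control participants are the less retained, the spurious difference runs from 3.5 to 9.2 points, against a planned effect of 15. A reader might infer that dropout could manufacture the whole planned effect; that needs extreme selection (employed retention of 40% vs 90% at p = 20% gives 15.4 points). Loss of 35% in each group that is unrelated to employment would cause no bias.

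**What to change.** 1. Describe the set as *available cases, analysed as allocated*.
2. Where t1 was missed, derive employment status at 12 months from the job start and end dates reported at t2. The follow-up questions now start from the exit interview, which has no meaning for someone who did not attend it; ask these participants about all jobs since study entry.
3. For those still missing, use multiple imputation by group with baseline covariates, t2 employment and, where consent exists, 12-month benefit status. Treat benefit status as an auxiliary variable only, since it is a partial proxy.
4. Prespecify a delta or tipping-point analysis of the primary result, with separate assumptions for each group. Do not rely on counting the missing as not employed.

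Cost: protocol wording, a changed prompt at t2, extra analysis, and possibly an amendment to the ethics committees and the registration. Attendance at t2 and consent to the records request are unknown, so recovery will be partial, and imputation helps only as far as these variables predict employment. The effectiveness analysis planned when t1 is complete may precede some t2 interviews, so its treatment of missing status should be stated too.
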